#### Rules for changing the study stage (Figure 2)

**Figure 2 f2:**
[figure not shown]
Rules for changing stages. SOF - sofosbuvir; ATV - atazanavir; DCV - daclatasvir.

If ATV and a presentation of DCV alone are effective and safe in the first stage, a second stage will be performed with the first- and second-best drugs from the previous stage combined according to the rate of decay of the viral load logarithm (slope). The drug with the highest decay rate will be administered first, followed by the drug with the second highest decay rate. The third phase will investigate the drug with the highest decay rate in Phase II/1 or Phase II/2.If only DCV presentations are effective and safe, a Phase II/2 trial will not be conducted, and Phase III will start with the formulation of DCV alone or combined with SOF which produces the higher rate of decay and it is safe according to the interpretation of the DSMB.If only ATV is effective and safe, a Phase II/2 will not be conducted, and Phase III starts with ATV alone.If none of the study drugs are effective and safe in Phase II/1, the study ends without conducting Phase II/2 and/or Phase III.

#### All participants’ daily routines will include

A clinical evaluation by the attending physician.Routine laboratory tests at the discretion of the attending physicians.Respiratory and motor physiotherapy.Surveillance of vital signs.Addition of ventilatory support measures, such as increased oxygen flow, use of noninvasive ventilation or high-flow nasal cannula, as recommended by the attending physicians.Prophylaxis of stress ulcers and venous thromboembolism according to the protocol of each institution.Transfer to advanced units (ward and ICU) according to the clinical judgment and patient’s need.The addition of other therapies, such as antibiotics, corticosteroids, IL-6 receptor inhibitors and other antivirals, as indicated by the attending physician.

### Study intervention compliance

- **Hospitalized patients:** Each dose of the study drug will be administered and supervised by a member of the clinical research team who is appropriately trained. The administration date and time will be entered into the case report form (CRF).- **Out-of-hospital patients:** Patients who are discharged before the end of treatment will have their drug dispensed for home use and be monitored by telephone interviews, a medication diary and physical reevaluation in return visits on the missing day from the 4 prespecified schedule times (baseline and Days - D - 3, 6 and 10). Assessments of study medication use will be performed at each study visit. The subject should be instructed to bring all unused study drugs to each visit and any empty bottles. The dates and number of tablets dispensed and returned must be recorded on the drug accountability form.

#### Drug accountability

The principal investigator at each site may delegate responsibility for study product accountability to the research pharmacist at the participating site. He/she will be responsible for maintaining complete records and documentation of study product receipt, accountability, dispensation, storage conditions, and final disposition of the study product(s). The time of study drug administration to the subject will be recorded on the appropriate data collection form (CRF). All study product(s), whether administered or not, must be documented on the appropriate study product accountability record or dispensing log available at the pharmacy of each center. The Coordinating Center team will verify the study product accountability records and dispensing logs of each participating site.

#### Concomitant therapy and drug interaction

Therapy administered before enrollment with any other experimental treatment or off-label use of marketed medications must be discontinued upon enrollment. Concomitant therapy will be recorded daily until D10. A subject cannot participate in another clinical trial or receive any experimental treatment other than the study drugs for the treatment of COVID-19. Some concomitant medications must be stopped or adjusted according to table 4 due to drug interactions.

**Table 4 t4:** Drug interactions

Drug	SOF	DCV	ATV	Effects	Action
Amiodarone	X	X	X	Bradycardia when administered with another antiviral	Do not administer. Switch to propafenone
Digoxin		X		↑Digoxin	Avoid administration. If necessary, decrease the dose by 30%
Quinidine		X	X	↑Quinidine	A dose adjustment is not needed (when not using ritonavir). Avoid use with DCV
Lidocaine			X		A dose adjustment is not needed (when not using ritonavir)
Carbamazepine	X	X	X	↓Efficacy SOF ↑Carbamazepine	Switch to 500mg of levetiracetam twice a day IV or VO
Phenytoin Phenobarbital				↓Efficacy ATV ↓Phenytoin ↓Phenobarbital	
Lamotrigine			X	↓Lamotrigine if administered with ritonavir	A dose adjustment is not needed (when not using ritonavir)
Rifampicin	X	X	X	↓Efficacy SOF and DCV	Do not administer or suspend RMP for 10 days
Itraconazole Ketoconazole Voriconazole		X X X	X X X	↑DCV ↑ATV ↑Itraconazole ↑Ketoconazole	Switch to amphotericin B
Dexamethasone		X		↓Efficacy DCV	Do not adjust dose. All patients will use this drug
Bosentan		X	X	↓Efficacy DCV	Switch to sildenafil at a dose of 25mg every 2 days
Dabigatran Rivaroxaban Apixaban		X	X	↑Dabigatran ↑Rivaroxaban ↑Apixaban	Substitute for enoxaparin
Warfarin	X	X	X	↑Warfarin	Monitor INR for a warfarin dose adjustment or switch to enoxaparin/heparin
Atorvastatin Pravastatin Simvastatin		X	X	↑Atorvastatin ↑Pravastatin ↑Simvastatin	Temporary suspension: risk of myopathy or statin dose reduction by 50%
Quetiapine			X	↑Quetiapine	Decrease quetiapine dose by 50%
Midazolam			X	↑Midazolam	Decrease midazolam dose by 50%
Ergot derivatives			X	↑Ergot derivatives	Suspend for 10 days
Omeprazole			X	↓Efficacy ATV	Switch to H2 antagonists. In case of gastrointestinal bleeding, maintain with the administration of the omeprazole dose with a difference of 12 hours from the ATV dose
Salmeterol			X	↑Salmeterol	Switch to formoterol or salbutamol
Sildenafil			X	↑Sildenafil	Reduce the dose of sildenafil to 25mg every 2 days
Tadalafil			X	↑Tadalafil	Reduce the tadalafil dose to 10mg every 72 hours
Antacids			X	↓Efficacy ATV	Administer 2 hours before or 1 hour after ATV
Tricyclic antidepressants Trazodone			X	↑Antidepressants ↑Trazodone	Decrease antidepressant doses by 50% Decrease the trazodone dose by 50%
Colchicine		X	X	↑Colchicine	Use a 0.6mg (1 capsule) dose followed by 0.3mg (1/2 tablet) 1 hour later. Do not readminister in less than 3 days
Diltiazem Nifedipine Verapamil		X	X	↑Diltiazem and DCV ↑Nifedipine and DCV ↑Verapamil and DCV	Reduce the diltiazem dose by 50% Reduce the nifedipine dose by 50% Reduce the verapamil dose by 50%
Famotidine Ranitidine Cimetidine			X	↓Efficacy ATV	Administer ATV 10 hours after and at least 2 hours before the famotidine dose Administer ATV 10 hours after and at least 2 hours before ranitidine dose Administer ATV 10 hours after and at least 2 hours before the cimetidine dose
Cyclosporine Tacrolimus Sirolimus			X	↑Cyclosporine ↑Tacrolimus ↑Sirolimus	Monitor serum level
Clarithromycin		X	X	↑DCV ↑ATV ↑Clarithromycin	Reduce the dose of clarithromycin by 50% (QTc prolongation) or use azithromycin
Oral contraceptives* containing ethinyl estradiol, norgestimate or norethindrone			X	↑Ethinyl estradiol ↑Norgestimate ↑Norethindrone	Exchange for desogestrel
Atazanavir		X		↑DCV only if using ritonavir	Do not change the dose Ritonavir will not be used
Fluticasone			X	↑Fluticasone	Switch to budesonide

DCV - daclatasvir; SOF - sofosbuvir; ATV - atazanavir; IV - intravenous; VO - oral; RMP - rifampicine; INR - International Normalized Ratio.

* Contraceptives: for patients in the sofosbuvir and daclatasvir groups, contraceptives with ethinyl estradiol will be provided. Patients participating in the atazanavir group will be provided contraceptives with desogestrel or gestodene.

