#### Interventions

Intervention drugs administered in each stage

**Phase II, first stage -** six arms with six different interventions will be designed:

ATV.DCV.SOF/DCV.PbO ATV.PbO DCV.PbO SOF/DCV.

**Phase II, second stage -** four arms with four different interventions will be designed:

Best of the first stage.Best of the first stage + the second best.PbO best first stage.PbO best first stage + PbO second best.

**Phase III, third stage -** two arms with two different interventions will be designed:

Best antiviral alone or in combination (defined in Stage 1 or 2).PbO best antiviral alone or in combination.

The doses and administration routes of the study drugs are described in table 3. If swallowing is impossible for any reason, the protocol provides for the use of the study drugs via a nasogastric or nasoenteral tube. The study drugs will be donated by pharmaceutical companies, with ATV (and PbO) donated by Fundação Oswaldo Cruz (Fiocruz) and DCV, SOF and respective PbOs donated by Blanver Farmoquímica e Farmacêutica.

**Table 3 t3:** Study drug dosage

Drug	Pharmaceutical form	Route of administration/ instructions for use	Frequency of administration	Conservation
Daclatasvir/placebo DCV	Coated tablets/ 28 tablets bottles*	Orally with or without food	2 tablets once daily on D1, 1 tablet once daily from D2 to D10	Room temperature 15 to 30°C
Sofosbuvir/placebo SOF	Coated tablets/ 28 tablets bottles*	Orally with or without food	1 tablet twice daily on D1, 1 tablet once daily from D2 to d10	Room temperature 15 to 30°C
Atazanavir/placebo ATV	Capsules with packs of 30 capsules*	Orally with food	2 capsules twice daily on D1, 1 capsule twice daily from D2 to d10	Room temperature 15 to 30°C

DCV - daclatasvir; SOF - sofosbuvir; ATV - atazanavir; D - day.

* Coated tablets for daclatasvir and sofosbuvir treatments and placebos and capsules for atazanavir treatment and placebo are identical in physical appearance.

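### The 12-hour separation that Table 4 requires between omeprazole and atazanavir in gastrointestinal bleeding cannot be kept under the twice-daily atazanavir schedule in Table 3

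*Protocol article*

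**What the plan says.** Table 3 of the protocol article (Interventions) sets the frequency for atazanavir and its placebo as "2 capsules twice daily on D1, 1 capsule twice daily from D2 to d10". The number of capsules changes after the first day, but the frequency is twice daily throughout.

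Table 4 (Concomitant therapy and drug interaction) marks omeprazole as interacting with ATV only and gives the effect as reduced ATV efficacy. The action begins "Switch to H2 antagonists. In case of gastrointestinal bleeding". In that event sites are to "maintain with the administration of the omeprazole dose with a difference of 12 hours from the ATV dose". The rule speaks of the ATV dose in the singular. Nothing in the article explains how the gap is to be kept with two ATV doses a day, and nothing exempts these patients from twice-daily dosing.

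**The concern.** A site caring for a bleeding patient allocated to ATV or its placebo holds two instructions from the same protocol. One fixes two ATV doses a day. The other asks for a separation that fits only a single daily dose. Taken literally, the second can bring omeprazole and ATV together, which is the situation the row is there to prevent.

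At stake are a rule that sites cannot follow in an acute situation and some loss of ATV effect in the patients concerned. Because treatment is blinded within each drug group, patients on ATV placebo fall under the same unworkable instruction, though they have no drug effect to lose. If ATV moves forward, the conflict goes with it into Phase II/2 or Phase III.

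**Working it through.** **Inputs**

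- ATV frequency: two doses per 24 hours, D1 to D10 (Table 3).
- Required separation between omeprazole and ATV in gastrointestinal bleeding: 12 hours (Table 4, omeprazole row).
- Interval between the two daily ATV doses: not stated. It is therefore varied below.

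**Reading 1: 12 hours from every ATV dose.** Put the ATV doses at 0 and *g* hours on a repeating 24-hour cycle, with *g* above 0 and at most 12. The longer ATV-free interval is 24 − *g* hours. The best place for omeprazole is its midpoint, so

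largest separation from the nearest ATV dose = (24 − *g*) / 2.

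| Gap *g* between the two ATV doses (h) | Largest separation (h) | Required (h) |
|---|---|---|
| 12 | (24 − 12)/2 = 6 | 12 |
| 10 | 7 | 12 |
| 8 | 8 | 12 |
| 6 | 9 | 12 |
| 4 | 10 | 12 |
| 2 | 11 | 12 |
| 1 | 11.5 | 12 |

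Twelve hours is reached only at *g* = 0, when the two doses are taken together and the schedule is no longer twice daily. No twice-daily timing meets the rule.

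**Reading 2: 12 hours from one ATV dose only.** Omeprazole given 12 hours after the dose at time 0 lies 12 − *g* hours from the other dose. With *g* = 12 this is 0 hours, so omeprazole coincides with the next ATV dose. With *g* = 10 it is 2 hours, and with *g* = 8 it is 4 hours. The rule can then be met in form, but at an even spacing it produces co-administration.

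**Comparison: the H2-antagonist row of the same table.** It reads "Administer ATV 10 hours after and at least 2 hours before the famotidine dose", with parallel wording for ranitidine and cimetidine. With ATV every 12 hours and the H2 antagonist *t* hours after an ATV dose, the rule needs *t* ≥ 2 and 12 − *t* ≥ 10. The solution is *t* = 2, since 2 + 10 = 12. That rule can be met, so the infeasibility is specific to the omeprazole row.

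**The case against.** The strongest reply is that the trigger is narrow. The default for omeprazole is a switch to H2 antagonists, whose spacing rule is feasible. The 12-hour rule applies only when a patient allocated to ATV or its placebo bleeds and is kept on omeprazole within a ten-day course. Table 3 also does not say that ATV is taken exactly every 12 hours, so 6 hours is not the only possible ceiling. Both points stand. They limit the reach of the problem but do not remove it, because no other twice-daily spacing reaches 12 hours from both doses.

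A reader might infer more than the documents support:

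- *That the H2-antagonist rule is also broken.* It leaves no slack under 12-hourly dosing, but it can be met. The article states no H2-antagonist frequency that would make it fail.
- *That the routine-care list contradicts Table 4.* The list includes "Prophylaxis of stress ulcers and venous thromboembolism according to the protocol of each institution". However, the section on concomitant therapy makes adjustment according to Table 4 mandatory for interacting drugs, and that specific rule governs the general list.
- *That the ATV slope comparison is diluted by a sizeable percentage.* If a fraction *q* of the planned 63 ATV patients (189 / 3) lost the whole effect, the slope difference would shrink by *q*. The documents give no value for *q*, and Table 4 says only that efficacy falls, not that it vanishes.
- *That the ranking tilts toward the daclatasvir arms.* Table 4 also lists dexamethasone as lowering daclatasvir efficacy and says that all patients will receive it. The net direction cannot be read from a rare omeprazole exception.
- *That a sensitivity analysis by spacing could be run on data already planned.* The article states clock times for study-drug doses. Concomitant therapy is recorded daily, with no stated time of administration.

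**Conclusion.** The contradiction between Table 3 and the omeprazole row of Table 4 is real and rests only on the protocol's own figures. The achievable separation is 6 hours under 12-hourly ATV, and below 12 hours for any twice-daily timing. Reading the rule as referring to a single dose leads to co-administration when doses are 12 hours apart.

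The point is minor. It concerns patients on ATV or its placebo with gastrointestinal bleeding who are kept on omeprazole. Any efficacy loss is confined to those on active ATV. Their number, the loss of ATV effect and the consequence for the viral-load slope cannot be derived from the documents. That the consequence is small is a judgement based on the narrow trigger, not a computed result. The documents do not support a claim that the Phase II/1 comparison or the choice of drug is materially biased.

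**What to change.** The sponsor should reconcile the ATV schedule in Table 3 with the omeprazole instruction in Table 4, so that sites have one rule that can be followed and that says how it applies when there is more than one ATV dose a day. Which schedule, interval or clinical rule to adopt is for the sponsor and its clinical advisers.

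The drafting effort is small, but the step is more than editorial. The article requires amendments to be approved by the ethics system (REC/Conep) before centres implement them. The article also reports 256 patients already randomized, against 252 planned for Phase II/1. The correction would therefore do little for that stage. It should be in place before any later stage that includes ATV. No change to the statistical analysis is needed.

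### Where a combination arm pairs atazanavir with a daclatasvir presentation, the Table 4 footnote gives its patients two different contraceptive supply instructions, one of which conflicts with the table's own atazanavir row

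*Protocol article*

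**What the plan says.** Table 4 (section Concomitant therapy and drug interaction) has a row headed "Oral contraceptives* containing ethinyl estradiol, norgestimate or norethindrone". It is marked in the ATV column only, shows the hormone levels as raised, and gives the action "Exchange for desogestrel".

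An asterisk on that row leads to a footnote about what the trial itself will supply. Its first sentence reads "for patients in the sofosbuvir and daclatasvir groups, contraceptives with ethinyl estradiol will be provided". Its second reads "Patients participating in the atazanavir group will be provided contraceptives with desogestrel or gestodene". There is no third sentence for a patient assigned ATV and DCV together.

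The design plans for such patients. Rules for changing the study stage (Figure 2) says "If ATV and a presentation of DCV alone are effective and safe in the first stage, a second stage will be performed", and the stage uses the two best drugs in combination. The Interventions section lists among the Phase II/2 arms "Best of the first stage + the second best" and its control, "PbO best first stage + PbO second best". It also lets a combination be the Phase III treatment.

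**The concern.** The footnote sorts patients as if each belonged to one drug group. That works in Phase II/1, where no arm holds both ATV and DCV. It stops working once an arm pairs them, because both sentences then describe the same patient and name different products.

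This is more than loose wording, because the table itself treats the difference as an interaction. For a patient on ATV plus DCV, the first footnote sentence supplies a product that the row above it tells sites to exchange. The eligibility criteria (Table 2) also exclude women of childbearing potential who will not agree to two contraceptive methods for 100 days, and the trial says it will provide the contraceptives. The footnote is therefore a supply instruction that pharmacies and sites would act on. What is at stake is consistent and safe handling of concomitant medication, not the statistical properties of the trial.

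**Working it through.** The plan gives no figure to reproduce here, so the check sets the passages side by side. It then counts when the conflict arises and which patients are under the instruction.

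**1. Instructions that apply, by assigned treatment**

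| Assigned treatment | Footnote, first sentence (ethinyl estradiol) | Footnote, second sentence (desogestrel or gestodene) | Table 4 row (exchange ethinyl estradiol) |
|---|---|---|---|
| DCV, or SOF/DCV | applies | – | – |
| ATV | – | applies | applies |
| ATV + DCV, or ATV + SOF/DCV | applies | applies | applies |

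Only the last line conflicts on the main point. The second line shows the lesser mismatch, which already exists in Phase II/1: the row names desogestrel, while the footnote names desogestrel or gestodene.

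**2. When the combination contains both drugs**

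Phase II/2 opens only if ATV and a DCV presentation are both effective and safe. The pair is then chosen by rank of viral-load decay rate (Rules for changing the study stage; Analysis of primary outcomes, Phase II/1). Ranking the effective treatments:

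- ATV and DCV effective: 2 orderings, both give ATV + DCV.
- ATV and SOF/DCV effective: 2 orderings, both give ATV + SOF/DCV.
- All three effective: 3! = 6 orderings. ATV is in the top two in 4. In the other 2 it ranks third, and the literal pair is DCV with SOF/DCV.

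Total: 2 + 2 + 6 = 10 orderings, of which 2 + 2 + 4 = 8 put ATV and a DCV presentation in one arm. This is a count of cases, not a probability. The conflict arises in the 8 and not in the other 2.

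**3. Reach to placebo**

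The Blinding section says that in Stages 1 and 2 the drug group may be known after randomization, but not whether the product is active or placebo. A site must therefore apply one contraceptive instruction to the active combination arm and its placebo arm alike. The same follows in Phase III, where the stage can be fully blinded.

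**4. Size of the arms concerned**

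Phase II/2 has 189 patients allocated 2:2:1:1. The active combination has 2/6 of the slots and its placebo 1/6:

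189 × (2/6 + 1/6) = 189 × 1/2 = 94.5.

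If the combination goes to Phase III, both arms of that stage are concerned: at least 189 and at most 564 patients under the Phase III section. These are arm sizes, not numbers affected. They include men and women who would not use a trial-provided contraceptive. The relevant subset cannot be computed from the document.

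**The case against.** The strongest reply is that the table body already gives the answer. Table 4 is organised by drug, the row is marked for ATV, and the text above it makes the table binding for interacting medication. On this view a site treating an ATV + DCV patient would follow the row, and would give the wrong supply only by ignoring both the row and the footnote's ATV sentence. The point has weight: the table is not silent on ATV-containing arms. It does not remove the conflict, because the footnote hangs on that same row and states what the trial will provide. A supply rule and an interaction rule then disagree, with no order of precedence.

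A second reply is that the group labels in the footnote mean the Stage 1 arms only. The footnote would then be silent on combinations, and the detail might sit in the full protocol, which is not shown. That reading is possible. However, Table 4 has its own row for atazanavir given with DCV, so co-administration was in view when the table was written. Under this reading too, the combination arm needs its own line.

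Two stronger inferences are tempting and should not be drawn. A reader might infer that every Phase II/2 combination arm holds both drugs. That is the evident intent, but pairing by rank allows DCV with SOF/DCV when all three treatments are effective and ATV ranks third; and the placebo combination arm holds neither drug. A reader might also take 94 or 95 patients, or 564, as the number at risk. Those figures are whole arms, 564 is a maximum, and all of it depends on earlier stages succeeding.

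It is also fair to say that the difference between desogestrel and desogestrel or gestodene is minor: the row speaks of an exchange and the footnote of supply.

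**Conclusion.** The point stands in conditional form. If the Phase II/2 combination, or a Phase III arm that carries it forward, pairs ATV with a DCV presentation, its patients meet both footnote sentences. The first of these conflicts with the oral-contraceptive row of the same table. Through blinding, the instruction also reaches the matching placebo arm.

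This rests on reading the footnote's group labels as covering anyone assigned the named drug. If they mean single-drug arms only, the defect is an omission, and the same correction is needed. The number of women concerned is unknown. There is no effect on sample size, power or type I error. The correction is worth making because it bears on patient safety and costs almost nothing. The naming difference between row and footnote for ATV patients is secondary.

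**What to change.** Reconcile the footnote with the Table 4 oral-contraceptive row in two respects:

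- State one instruction for any arm that contains both ATV and a DCV presentation, and for its placebo, in Phase II/2 and in Phase III if the combination is carried forward.
- Make the row and the footnote name the same products for ATV-containing arms.

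Which product is right is a clinical decision for the sponsor, and none is proposed here. The cost is about one line in the footnote, with the same wording carried into any site or pharmacy instructions derived from it. No analysis, sample size or randomization element changes.
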